### Data collection and monitoring

2.14

In this 24-week trial, all participants will be treated with SGF or SGF placebo for 12 weeks and followed up for another 12 weeks. All data will be entered into the designated database that will be exclusively managed by the research team members. Electronic data files, including databases, analysis programs, analysis results, and explanatory files, will be classified and stored in multiple backups on different recording media and properly stored to prevent damage. All of the original files shall be kept in accordance with the unified requirements of scientific research management, and the management data shall be transmitted in time.

### Quality control

2.15

Longhua Hospital affiliated with Shanghai University of Traditional Chinese Medicine (http://www.longhua.net/ywsy/gzlc/287.jhtml) is responsible for quality control and training for all investigators. All team members of the trial will receive systematic training to completely apprehend the study procedures. The person in charge will regularly inspect the subjects, identify the problem, corrects it in time, and cancel a researcher's qualification when the problem is serious. The monitor will regularly monitor the study and discuss with the investigator its progress, the CRF and the original records, and the accuracy of the data records.

### Statistical analysis

2.16

The statistical analysis will be performed using SPSS 20.0. If the measurement data are normally distributed with homogeneous variance, the mean ± standard (± s) will be used for the statistical analysis and the t-test will be used for the intergroup comparisons. If the data do not follow a normal distribution, the rank sum test will be used to make statistical inferences. Enumeration data will be statistically described as frequency, constituent ratio, and rate. Comparison of indicators with dichotomous or multi-classification disorders will be performed using the *χ*^2^ test. The rank sum test will be used to compare groups of ordered classification analysis indicators. Statistical significance will be set at *P* < .05.

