This randomized double-blind placebo-controlled clinical trial of DHF will include 12 weeks of clinical intervention and 12 weeks of follow-up. Changes in plasma N-terminal brain natriuretic peptide precursor (NT-proBNP) before versus after treatment will be the primary outcome measure. Changes in cardiac ultrasound, cardiopulmonary exercise test, cardiac function grade, TCM syndrome score and Minnesota Heart Failure Quality of Life Scale will be the secondary outcome measure. We will also assess its safety aspects by thoroughly documenting any adverse events (AEs) that occur.

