#### Primary outcomes

2.9.1

NT-proBNP levels will be determined using an enzyme-linked immunosorbent assay kit before and after drug administration (week 0 and week 12).

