### Sample size

2.13

One study^[15]^ showed that HF patients whose NT-proBNP levels decreased by more than 30% had better clinical prognosis. In this study, it was estimated that the decrease in plasma NT-proBNP in the treatment group after treatment would reach 42%. Formula n^[16]^$n={\left[\frac{\left(u_{\alpha }+u_{\beta }\right)}{\delta /\sigma }\right]}^{2}+\frac{1}{2}u_{\alpha }^{2}$ was calculated according to the sample size, where standard deviation (instead of σ) is set to 30%, α = 0.05, uα = 1.645, β = 0.1, uβ = 1.282, and δ = 42–30 = 12.

The sample size was calculated as 54 cases, considering a withdrawal rate of no more than 20%, the sample size of this study was determined to be 130 people with a ratio of the experimental and control groups of 1:1 for 65 people in each group.

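### The primary NT-proBNP comparison uses a test picked after a normality and variance check and does not adjust for week-0 NT-proBNP as a covariate; a pre-specified log-scale ANCOVA would gain some precision at almost no cost

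*Protocol article*

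**What the plan says.** The Introduction defines the primary outcome as a change: "Changes in plasma N-terminal brain natriuretic peptide precursor (NT-proBNP) before versus after treatment will be the primary outcome measure". Section 2.9.1 puts the assay at weeks 0 and 12, so a baseline value is planned for every patient.

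Section 2.16 gives one rule for all continuous outcomes, with no separate rule for the primary one. The first branch applies on the condition "If the measurement data are normally distributed with homogeneous variance", and then "the t-test will be used for the intergroup comparisons". The second branch reads: "If the data do not follow a normal distribution, the rank sum test will be used to make statistical inferences". No covariate, transformation or model is named. Significance is set at P < .05 without stating one- or two-sided.

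Section 2.13 plans on percentage falls in NT-proBNP: 42% against 30%, a difference of 12 with an SD of 30, and "α = 0.05, uα = 1.645", which is a one-sided quantile.

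**The concern.** Three features of the rule in 2.16 bear on the single primary outcome.

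- The test is not fixed until the data have been inspected.
- The rule is incomplete. Data judged normal but with unequal variances satisfy neither condition, so no test is assigned.
- Week-0 NT-proBNP is used only by subtraction. Subtraction forces a coefficient of 1 on baseline. Unless week 0 and week 12 are almost perfectly correlated, that is not the best coefficient, and some chance baseline imbalance remains in the comparison as noise.

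At stake is precision on the primary endpoint, in a trial whose planned numbers leave little to spare. Both measurements needed for the better analysis are already in the schedule.

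**Working it through.** **1. The plan's own figure.** Section 2.13 prints n = [(uα + uβ)/(δ/σ)]² + uα²/2. With uα = 1.645, uβ = 1.282, δ = 12 and σ = 30:

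(2.927/0.4)² + 1.645²/2 = 53.55 + 1.35 = 54.9

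The article states 54, and 54 × 1.2 = 64.8 gives 65 per group. With 20% withdrawal, 65 × 0.8 = 52 per arm remain.

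**2. Variance factor.** Let both visits have variance S² and correlation r, on the same scale.

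- Change score: Var = 2S²(1 − r)
- ANCOVA residual: Var = S²(1 − r²)
- Ratio: (1 − r²)/[2(1 − r)] = (1 + r)/2

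| r (assumed) | Variance ratio | Equivalent extra patients |
|---|---|---|
| 0.5 | 0.75 | 1/0.75 = 1.33, so 33% |
| 0.8 | 0.90 | 1/0.90 = 1.11, so 11% |

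**3. Power with the section 2.13 inputs.** Take 30 as the SD of change, with two arms, two-sided 5% and 52 per arm.

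- Unadjusted: 12/(30 × √(2/52)) = 2.04, and Φ(2.04 − 1.96) = 53% (about 52% with the t distribution)
- ANCOVA, r = 0.5: 2.04/√0.75 = 2.36, and Φ(0.40) ≈ 65%
- ANCOVA, r = 0.8: 2.04/√0.90 = 2.15, and Φ(0.19) ≈ 57%

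With all 65 per arm retained, unadjusted power is 63%. ANCOVA gives 81% at r = 0.3, falling to 65% at r = 0.9. No r in that range reaches the planned 90%.

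**4. Simulation of the rule at the planned effect.** Falls of 42% and 30% imply a ratio of 0.58/0.70 = 0.83, reading the 30% as the placebo fall. Assumed: log-normal NT-proBNP, log SD 0.9, 52 per arm, and a normality check followed by a t-test or rank sum test on percent change.

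| r (assumed) | Rule in 2.16 on percent change | Log-scale ANCOVA |
|---|---|---|
| 0.5 | about 18% | about 23% |
| 0.6 | about 21% | about 27% |
| 0.7 | about 27% | about 31% |
| 0.8 | about 37% | about 41% |

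Allowing for simulation error, the gain is about 3–6 percentage points. These power levels are lower than in step 3 because the assumed spread is larger relative to the effect. At r = 0.5 the SD of the log ratio is 0.9 × √(2 × 0.5) = 0.9, against an effect of |ln 0.83| ≈ 0.19, a standardised effect of about 0.21 rather than 12/30 = 0.40. The difference between the columns carries the argument, not their level.

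**5. Type I error.** Under no effect, the rule's rejection rate stayed at about 4–6% in the simulations, as did that of ANCOVA.

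**The case against.** The strongest reply is that a t-test or rank sum test on change is valid under randomisation, and that covariates and transformations are often left to an analysis plan, which is not shown. The validity part stands: nothing here biases the comparison. The second part stands only in part, because section 2.16 does not stay silent. It names the tests and the condition for choosing between them, and that condition leaves a gap.

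Several stronger readings may tempt a reader, and the document does not support them:

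- **That the plan ignores baseline.** The outcome is a change, so baseline is used by subtraction. What is missing is adjustment as a covariate.
- **That choosing the test from the data inflates false positives.** The simulations show no such inflation. Under the log-normal model percent change almost always fails the normality check, so the choice is nearly predetermined.
- **That the rank sum test can give no percent-scale estimate.** Ranks of percent change are the ranks of the log ratio, so a Hodges-Lehmann shift on the log ratio yields an SGF/placebo ratio with an interval. Section 2.16 does not exclude this.
- **That the gain is large.** Taking absolute change as the comparator, or an effect bigger than the planned 0.83, makes the contrast look wider. Section 2.13 plans in percent, so percent change at 0.83 is the fair comparison.
- **That ANCOVA rescues the power.** It does not; see step 3 of the working.

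It is also fair to say that r, the log SD and the skewness of NT-proBNP are nowhere in the document. The direction of the gain is secure; its size is not.

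**Conclusion.** The point holds as an improvement in efficiency and pre-specification, not as an error that invalidates the trial. Section 2.16 fixes an incomplete, data-dependent choice between two tests that are not baseline-adjusted, where a single baseline-adjusted analysis would be at least as precise for any r below 1.

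On the section 2.13 inputs at 52 per arm, the gain is about 12 points of power at r = 0.5 and 4 to 5 points at r = 0.8. In the log-normal simulation it is about 3–6 points.

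These figures rest on assumed correlations, on equal variances at the two visits, on reading the SD of 30 as the SD of change, and, for the simulation, on log SD 0.9 and a 30% placebo fall. The shortfall in sample size is a separate matter and remains.

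**What to change.** In section 2.16, state the primary analysis as ANCOVA of log(week-12 NT-proBNP) on treatment and log(week-0 NT-proBNP), at two-sided 5%. Report the SGF/placebo ratio of geometric means with its 95% confidence interval; one minus the ratio is the percent difference. Remove the normality and variance check for the primary outcome, which also closes the unequal-variance gap. Keep the rank sum test on the log ratio of week 12 to week 0 as a sensitivity analysis.

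The cost is a few lines of text and one degree of freedom. No visit, assay or patient is added, and SPSS, the software already named, fits the model. The change should be made before unblinding.

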## Discussion

3

HF, the final stage of many heart diseases, is a worldwide problem. The report mentioned that mortality, hospitalization, and rehospitalization rates remained high in HF patients.^[17]^ The 2016 ESC Guidelines^[18]^ highlighted the ejection fraction preservation in the diagnosis of HF, suggesting that we must pay more attention to the status of patients with DHF. There is currently no clear and effective drug for the treatment of DHF, and high-quality clinical trials on this disease treated by TCM are lacking. SGF is a TCM that has been used for hundreds of years owing to its unique theoretical connotation and practical effect, but its clinical efficacy and safety have not been systematically evaluated in randomized controlled trials.

A query of PubMed, Web of Science, Embase, the Cochrane Library, Wan Fang Database, and Clinical Trials for publications through February 2021 revealed no data about the efficacy or safety of SGF for treating DHF patients. Therefore, this study will be the first randomized double-blind placebo-controlled study to evaluate the efficacy and safety of the SGF in the treatment of patients with DHF.

The results of this study will not only prove the exact efficacy of SGF on DHF, also it will document changes in SGF on quality of life through follow-up. This clinical trial will provide powerful evidence to provide a safe and effective reference for future research.
